### Lifestyle intervention

The Lifestyle Intervention is an evidence-based approach utilizing culturally and linguistically modified, motivationally targeted, individually-tailored intervention materials developed in our prior randomised controlled trials among Hispanics [32-39]. The intervention draws from Social Cognitive Theory [40] and the Transtheoretical Model [41] and takes into account findings by our research group on the specific social, cultural, economic, and environmental resources as well as challenges faced by women of Hispanic backgrounds [25,42,43].

The Introductory Phase (~29 weeks gestation - delivery) (Figure 1) will start with a face-to-face session. The goal of this phase is to optimize gestational weight gain for the remaining pregnancy period and move women over the continuum of pre-contemplation to contemplation and preparation for the postpartum Active Intervention Phase. Motivational interviewing principles will be used to identify and strengthen women’s motivations for change. Specifically, the session will target knowledge and attitudes regarding gestational weight gain, postpartum weight loss, and type 2 diabetes prevention. Gestational weight gain guidelines will be reviewed and participants will be provided with a digital scale.

The session will additionally include administration of diet and physical activity questionnaires that facilitate tailoring the intervention. The Diet Tailoring Questionnaire is a two-part survey consisting of a checklist of high-calorie and lower-calorie foods and beverages commonly consumed by the target population. Respondents are asked to indicate the frequency that they consume the various foods and rate their confidence (self-efficacy) in their ability to decrease high calorie and increase low calorie food consumption. The Exercise Tailoring Questionnaire consists of 3 measures: Stages of Change for Physical Activity [44], Processes of Change for Physical Activity [45], and Self-Efficacy for Physical Activity [44].

This session will be followed by a third trimester booster telephone counseling session which will review progress toward gestational weight gain management and reinforce preparation for postpartum weight loss. Print-based intervention materials, in Spanish or English depending upon participant preference and written at a 6th grade reading level, will be mailed.

The Active Phase (6 weeks postpartum – 6 months postpartum) (Figure 1) will start with a face-to-face session. The tailoring questionnaires will be repeated and counseling will include the development of individualized weight loss, physical activity, and dietary goals. This session will be followed by weekly, biweekly, and monthly mailed, print-based materials as well as telephone booster calls to provide motivationally-based individualized feedback. Specifically, mailed materials are culturally modified, individually-tailored and motivationally targeted based on responses to monthly mailed tailoring questionnaires. Booster telephone sessions facilitate: 1) review of progress toward dietary, physical activity and weight loss goals, 2) problem-solving of challenges faced in achieving goals (e.g., balancing caregiver/household responsibilities, cultural norms of self-sacrifice, limited social support, partner negotiation, and neighborhood safety), 3) discussion of mailed tip sheets, and 4) assistance with setting new goals.

The Maintenance Phase (6 – 12 months postpartum) (Figure 1) will involve continued telephone sessions and mailed materials on a monthly and then bimonthly schedule.

### Curriculum

At the outset of the Active Phase of the intervention, a weight-loss goal based on prepregnancy BMI will be set and participants will be encouraged to work toward this goal by focusing on a reduction of 1-2 pounds per week. The health educator will utilize a checklist of motivators for wanting to lose weight, specific to new mothers, to help women identify their own weight loss motivations and to reinforce engagement. Participants will be encouraged to weigh themselves at home daily and to chart their weight on a grid weekly.

Physical activity change will be targeted via individualized week-by-week goals that focus on increasing the time spent in moderate intensity activity, as well as steps taken per day.

Women will choose what form of safe activity they enjoy the most or can most readily fit into their lifestyle, from dancing to walking in a shopping mall to yard work. The accumulation of short bouts (i.e., 10 min episodes) will be encouraged. Pedometers and activity logs will be provided for women to monitor their activity. Based on responses to the tailoring questionnaires, individually-tailored computer Expert-System Feedback Reports [37,39,46,47] will draw particular messages from a library of approximately 296 messages regarding motivation, self-efficacy, and cognitive and behavioral strategies for exercise adoption. Stage-Matched Manuals will focus on the benefits of exercise, building social support for new behavioral patterns, and strategies for overcoming barriers to exercise specific to low-income Hispanic women. Tip Sheets include topics such as stretching and exercising with baby (e.g., walking while pushing a stroller).

Dietary change will be targeted by working toward an ultimate goal of 1,500 calories per day (up to 2,000 for breastfeeding women who lose more than 2 lbs/week over a 2 week period). Dietary goals will be tailored to the participant based on responses to the Diet Tailoring Questionnaires, which take into consideration energy-dense foods that the participant eats frequently and feels confident that she is able to reduce or replace, and lower calorie foods which the participant eats infrequently and feels confident that she can increase. Participants will be instructed in how to self-monitor dietary intake using the food calorie guide and a tip sheet for measuring portion sizes. Participants will be provided with measuring cups and a dietary log.

Quality control procedures will ensure that stage of change and social cognitive constructs are consistently represented in all intervention materials.

### Health & wellness (control) intervention

To ensure retention and to control for contact time, the Health & Wellness (control) arm will receive mailed health materials and telephone booster calls on the same schedule as the Lifestyle Intervention arm. Mailed materials focus on non-exercise and non-dietary topics and include booklets from ACOG and the American Academy of Pediatrics in English or Spanish. These booklets represent high-quality, standard, low-cost, self-help material currently available to the public. In this way, we control for contact time, while keeping the content of the two interventions distinct. Hispanic control-arm participants in our prior studies reported that these materials were of interest and differential dropout did not occur between study arms [36,48].

### Outcome variables

Postpartum weight loss will be measured as the difference between weight at 6 or 12 months postpartum and weight at delivery, and will be calculated as absolute weight change according to prepregnancy BMI, percentage who retain a specific amount of weight over prepregnancy weight, or proportion whose BMI category changes from prepregnancy BMI category as have others (Table 1) [12-14].

**Table 1 T1:** Variables collected at assessment time points

	**Pregnancy**	**Postpartum**		
	**3rd trimester**	**6 wks**	**6 mos**	**12 mos**
**Aim #1: Postpartum weight loss**	X	X	X	X

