### Aims

Specific aims are to achieve the Institute of Medicine (IOM) guidelines for postpartum weight loss and to improve maternal metabolic status by achieving and maintaining 1) postpartum weight reduction to prepregnancy weight if prepregnancy BMI was in the normal range, or to achieve a 5% reduction from prepregnancy weight if prepregnancy BMI was overweight/obese [27]; 2) at least 150 min per week of moderate intensity physical activity such as brisk walking, as recommended by ACOG for the postpartum period [28]; and 3) reduction in postpartum total energy intake via reduced consumption of popular energy-dense foods (e.g., fast food, high-fat snacks, fried foods and sugar-sweetened beverages), reduced portion size, appropriate modifications in ethnic recipes, and higher fruit and vegetable intake, as recommended by the ADA [29].

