### Data analysis

Primary analyses will evaluate differences in the change from 6 weeks postpartum to 12 months postpartum between the groups (an intent to treat analysis) in postpartum weight loss (aim #1), biomarkers of insulin resistance (aim #2), and biomarkers of cardiovascular disease risk (aim #3). We will use mixed models with random subject effects, including a common mean at baseline for the treatment groups, a period effect, and an intervention by period interaction [60]. The mixed model analysis will enable inclusion of time varying covariates such as breastfeeding behaviors, depression, and sleep, which may vary between baseline and follow-up for individuals. Equivalence of treatment groups will be assessed by comparing distributions of the potential confounders across groups. In addition, we will investigate established risk factors for type 2 diabetes as potential confounders or effect modifiers. Important potential effect modifiers include prepregnancy BMI, and breastfeeding behaviors. Mixed model analyses will also be used to account for the repeated measures of exercise and diet and will be used to evaluate adoption and maintenance of behavior change (aim #4) in the Lifestyle Intervention group.

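### Aim #1 weight change starts at delivery, at 6 weeks or at baseline depending on the section, and the first two starting points fall after randomisation and the prenatal intervention

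*Protocol article*

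**What the plan says.** Four sections of the Protocol article bear on the starting point for Aim #1.

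- **Outcome variables** starts at delivery: "Postpartum weight loss will be measured as the difference between weight at 6 or 12 months postpartum and weight at delivery".
- **Data analysis** starts at 6 weeks: "Primary analyses will evaluate differences in the change from 6 weeks postpartum to 12 months postpartum between the groups". The mixed model in the same section is described as "including a common mean at baseline for the treatment groups".
- **Power and sample size** is built on the between-arm difference in change from baseline. The Recruitment and Randomisation sections place the baseline assessment at enrolment and complete it before randomisation at about 29 weeks.
- **Aims** sets each woman's target against her weight before pregnancy, for example "postpartum weight reduction to prepregnancy weight if prepregnancy BMI was in the normal range".

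The Lifestyle intervention section describes an Introductory Phase from about 29 weeks to delivery: "The goal of this phase is to optimize gestational weight gain for the remaining pregnancy period". Table 1 schedules weight in the third trimester and at 6 weeks, 6 months and 12 months postpartum.

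**The concern.** Two analysts who followed Outcome variables and Data analysis respectively would estimate different quantities for the same aim, and neither would be estimating the one used for the sample size. This is a conflict between stated definitions, so it is more than detail left to a fuller document.

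The choice also affects validity. Randomisation makes the arms comparable in expectation at enrolment. At delivery and at 6 weeks the Lifestyle arm has already been through a phase directed at weight gain. A change score that starts there removes whatever that phase achieved, although it is part of the randomised intervention. A woman who gained less before delivery has less to lose afterwards.

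**Working it through.** **Inputs.** From Power and sample size: 0.35 to 0.40 SD, 80% power, 0.05 significance level, 128 per arm, 15% attrition, 300 recruited. From Randomisation: about 29 weeks. The effect g on weight at the reference time is an assumption, because the documents give no figure for it.

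**1. The plan's own figure.** For a two-sided 0.05 test at 0.35 SD, n per arm = 2 × (1.960 + 0.8416)² / 0.35² = 2 × 7.849 / 0.1225 = 128.1. This rounds up to 129, or 258 in total against the stated 256. A one-sided test would need only 101 per arm, so the two-sided reading is the one that fits. For attrition, 256 / 0.85 = 301.2, or 302 against the stated 300. The sample size reproduces within rounding.

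**2. What each reference estimates.** Let mean weight at the reference time be R in the control arm and R − g in the Lifestyle arm. Let mean weight at 12 months be W and W − d.

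- Control loss = R − W.
- Lifestyle loss = (R − g) − (W − d) = R − W + d − g.
- Between-arm difference in loss = d − g.

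At enrolment, g is zero in expectation because of randomisation, and the difference is d. At delivery or 6 weeks, g is whatever the prenatal phase has produced by then.

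**3. Illustrative size.** Take a true 12-month benefit d = 0.35 SD, 128 per arm and the SD of change held at 1. The standard error is √(2/128) = 0.125 and power is Φ((d − g)/0.125 − 1.96).

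| Assumed g (SD) | Effect d − g (SD) | (d − g)/0.125 | Power |
|---|---|---|---|
| 0 | 0.35 | 2.80 | 80% |
| 0.05 | 0.30 | 2.40 | 67% |
| 0.10 | 0.25 | 2.00 | 52% |
| 0.15 | 0.20 | 1.60 | 36% |

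**4. The baseline constraint in the mixed model.** Giving both arms one baseline mean is justified by randomisation only at a time before randomisation.

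- If baseline means enrolment, the constraint is sound. The stated 6-week-to-12-month contrast is then not change from that baseline, and it still estimates d − g.
- If baseline means 6 weeks, the model forces equality at a time when the arms have already been treated differently. With two time points this acts like adjustment for 6-week weight and gives roughly d − b·g, where b is the slope of 12-month on 6-week weight. Part or all of the prenatal effect is again removed.

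**The case against.** The strongest reply is that Data analysis names the primary contrast and fixes it at 6 weeks to 12 months, so the delivery definition is only descriptive. Six weeks is also when the Active Phase begins, which makes it a natural start for postpartum weight loss. On this reading the sections could be aligned by a wording change. It is true that the delivery reference is not what the primary analysis states. The reply does not rescue the 6-week reference, which also follows randomisation and the prenatal phase and is open to the same subtraction. Change from 6 weeks answers a reasonable question about the Active Phase onward, but not the intention-to-treat question about the whole randomised intervention.

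A second reply concerns size. The plan speaks of optimising gestational weight gain, not reducing it, and the prenatal phase is one face-to-face session, one telephone call and mailed materials. The value of g may be small. It could even be negative, in which case a post-randomisation reference would flatter the intervention. This stands: the power figures are illustrations, not predictions.

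Three stronger readings may tempt a reader, and the documents do not support them.

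- **Reversed sign.** A reader might infer that the arm ending lighter would appear to do worse. That needs g to exceed d, so that the Lifestyle arm truly lost less after the reference time. Nothing in the article suggests this is likely.
- **Free choice of outcome.** The outcome is "calculated as absolute weight change according to prepregnancy BMI, percentage who retain a specific amount of weight over prepregnancy weight, or proportion whose BMI category" change, with the forms joined by an or. A reader might infer that one could be picked after seeing the data. However, the mixed model points to continuous weight, Data analysis fixes 12 months, and ranking the supporting forms is commonly left to a full protocol or SAP. For the same reason no information loss from dichotomising can be sized here.
- **No usable delivery weight.** Table 1 has no delivery column, but it lists study assessments, and the Covariates section says weight is recorded at every prenatal visit. The objection to delivery weight is its timing.

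**Conclusion.** The point holds. Outcome variables, Data analysis, and Power and sample size give three incompatible references for Aim #1 weight change, and two of them are post-randomisation values that the prenatal phase can move. The d − g result is algebra and does not depend on assumed figures; the size of the loss does. With d = 0.35 SD, 128 per arm and SD of change 1, power falls from about 80% to about 52% if g is 0.10 SD and to about 36% if g is 0.15 SD. If g is zero, nothing is lost, but the sections still conflict. The stated sample size is arithmetically sound for a 0.35 SD difference on whichever contrast is chosen.

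**What to change.** Align Outcome variables, Data analysis, and Power and sample size on one primary Aim #1 contrast: the between-arm difference in measured weight at 12 months postpartum relative to enrolment weight, which precedes randomisation. Either of two analyses serves:

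- ANCOVA of 12-month weight on enrolment weight; or
- the planned mixed model, with baseline stated to be the enrolment assessment and the treatment effect read at 12 months.

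Adjustment for prepregnancy weight may be added. Drop delivery weight and 6-week weight as the primary reference. Report change from 6 weeks, 6-month weight, weight retained over prepregnancy weight, and BMI-category change as secondary outcomes.

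The cost is a wording change, and those versions lose primary status. No new data are needed: Table 1 already schedules third-trimester and 12-month weight, and the prepregnancy-referenced forms already require prepregnancy weight.

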**Aim #2: Postpartum biomarkers of insulin resistance**				
Glucose	X	X	X	X
Insulin	X	X	X	X
HbA1c	X	X	X	X
Adiponectin	X	X	X	X
Leptin	X	X	X	X
TNF-α	X	X	X	X
HOMA	X	X	X	X
Area-Under-The-Glucose Curve (AUC)	X	X	X	X
**Aim #3: Other postpartum biomarkers of cardiovascular risk**				
Total cholesterol	X	X	X	X
Triglycerides	X	X	X	X
HDL-Cholesterol	X	X	X	X
LDL-Cholesterol	X	X	X	X
Systolic blood pressure	X	X	X	X
Diastolic blood pressure	X	X	X	X
CRP	X	X	X	X
Fetuin-A	X	X	X	X
Albumin-to-creatinine ratio (ACR),	X			
**Aim #4: Behavioral outcomes**				
Physical activity (actigraph, PPAQ)	X	X	X	X
Dietary intake (24-hr recalls)	X	X	X	X
**Censoring variables**				
Postpartumpregnancy test (urine)		X	X	X
75 g OGTT (postpartum)		X	X	X
**Eligibility variables**				
100 g OGTT (prenatal)	X			
**Covariates**				
Clinical characteristics of the current pregnancy	X			
Gestational weight gain	X			
Medical history	X			
Sociodemographic factors	X			
Smoking (Cotinine) and substance use	X	X	X	X
Postpartum factors (e.g., sleep, depression, breastfeeding)		X	X	X

Fasting biomarkers will be collected at baseline, and at 6-weeks, 6-months, and 1-year postpartum (Table 1). Postpartum biomarkers of insulin resistance will include glucose, insulin, HbA_1c_, leptin, TNF-α, HOMA, Area-Under-The-Glucose Curve (AUC), and adiponectin. Postpartum biomarkers of cardiovascular risk factors will include blood lipids, blood pressure, C-reactive protein (CRP), fetuin-A, and albumin-to-creatinine ratio (ACR). Postpartum diabetes screening will occur at each postpartum assessment and will follow the guidelines of the 2007 5th International Workshop Conference on GDM recommending a postpartum 75-g OGTT [49] using diagnostic criteria defined by the American Diabetes Association [31].

### Behavioral outcomes

Women will be provided with the ActiGraph GT3X-plus activity monitor to be worn on the wrist for 7-days at each of the assessment time periods (enrollment, 6-weeks, 6-months, and 12-months postpartum). Previous studies have reported reasonable validity under laboratory conditions among pregnant women [50], as well as under free-living conditions [51-53]. In addition, at each assessment time period, trained bilingual personnel blinded to the assigned intervention arm will conduct three unannounced 24-hr dietary recalls over a two-week period and administer the Pregnancy Physical Activity Questionnaire (PPAQ) [54]. The PPAQ is a semi-quantitative questionnaire which evaluates participation in household/caregiving, occupational, sports/exercise, and transportation activities.

### Covariates

Clinical characteristics of the current pregnancy and medical history will be abstracted from the pregnancy medical record (Table 1). Weight is measured prospectively at each prenatal visit and postpartum weight will be measured during assessment visits by trained study staff to the nearest 0.1 kg on accurately calibrated standard clinical scales using a standardized protocol. Gestational age will be based upon the best clinical estimate as recorded in the medical record. Adherence with gestational weight gain guidelines will be calculated by comparing the observed weight gain with the 2009 IOM Guidelines [27]. We will also collect gestational age at the time of GDM screen; degree of abnormality on glucose tolerance testing during pregnancy; treatment for glucose abnormality during pregnancy (e.g., diet, oral hypoglycemic agents and/or insulin); pregnancy complications; and birth outcomes.

Sociodemographic factors will be collected via self-report at enrollment. Acculturation will be assessed via the Psychological Acculturation Scale [55], language preference, and generation in the U.S. Smoking will also be assessed via the biomarker cotinine. Postpartum factors will be collected via self-report at each postpartum assessment and will include: The Pittsburgh Sleep Quality Index (PSQI) [56], the Edinburgh Postpartum Depression Scale [57,58], and the Infant Feeding Questionnaire [59].

### Data analysis

Primary analyses will evaluate differences in the change from 6 weeks postpartum to 12 months postpartum between the groups (an intent to treat analysis) in postpartum weight loss (aim #1), biomarkers of insulin resistance (aim #2), and biomarkers of cardiovascular disease risk (aim #3). We will use mixed models with random subject effects, including a common mean at baseline for the treatment groups, a period effect, and an intervention by period interaction [60]. The mixed model analysis will enable inclusion of time varying covariates such as breastfeeding behaviors, depression, and sleep, which may vary between baseline and follow-up for individuals. Equivalence of treatment groups will be assessed by comparing distributions of the potential confounders across groups. In addition, we will investigate established risk factors for type 2 diabetes as potential confounders or effect modifiers. Important potential effect modifiers include prepregnancy BMI, and breastfeeding behaviors. Mixed model analyses will also be used to account for the repeated measures of exercise and diet and will be used to evaluate adoption and maintenance of behavior change (aim #4) in the Lifestyle Intervention group.

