## Methods

Estudio Parto (Project Aiming to Reduce Type twO diabetes) will be based at the ambulatory obstetrical practices of Baystate Medical Center in Western Massachusetts. Eligible pregnant Hispanic women who screen positive for GDM will be recruited between 24-28 weeks gestation and randomly assigned to a Lifestyle Intervention (n = 150) or a Health & Wellness (control) Intervention (n = 150). Multimodal contacts (i.e., in-person, telephone counseling, and mailed print-based materials) will be used to deliver the intervention from late pregnancy (29 weeks gestation) to 12 months postpartum, encompassing introductory, active, and maintenance phases (Figure 1).

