### Recruitment

The trial will capitalize on our expertise in culturally appropriate strategies for recruiting pregnant Hispanic women in practice-based settings [30]. Specifically, bilingual (Spanish and English) and bicultural health educators will recruit women at the time of routine GDM screening. Women will be informed of the aims and procedures of the project and will be asked to sign a written informed consent form, as approved by the Institutional Review Boards of the University of Massachusetts-Amherst and Baystate Health. Upon enrollment, the baseline assessment will be conducted which includes: 1) data collection of behaviors during pregnancy via standardized questionnaires, 2) measures of physical activity via an ActiGraph GT3X-plus activity monitor (Actigraph LLC, Pensacola, FL) to be worn on the wrist for the next 7 days, 3) measures of dietary intake via three unannounced 24-hr dietary recalls over the following two-week period, 4) laboratory measures of biomarkers of insulin resistance and cardiovascular risk via a study-specific fasting blood sample. Completion of each assessment and blood draw is followed by a gift card.

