### Randomisation

Randomisation to the Lifestyle Intervention or to the Health & Wellness (control) Intervention will occur at ~29 weeks gestation, after completion of the baseline assessment. Randomisation will be stratified based on the results of the diagnostic 100-g OGTT using thresholds defined by the American Diabetes Association (ADA) [31] (≥ 95 mg/dL fasting and?≥?180 mg/dL, ≥155 mg/dL and ≥140 mg/dL at 1 hour, 2 hours and 3 hours, respectively): 1) no glucose values meeting or exceeding the ADA thresholds; or 2) one or more glucose values meeting or exceeding the ADA thresholds.

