### Power and sample size

The study is powered to detect mean differences in change in outcome variables from baseline in the Lifestyle Intervention as compared to the Health and Wellness (control) Intervention that are equivalent to 0.35 to 0.40 standard deviations, or a “small-medium” effect size [61], at 80% power at a 0.05 level of significance. A total of 256 women are required (128 participants per study arm). With an expected attrition rate of 15%, 300 eligible women will be recruited.

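### The primary contrast runs from 6 weeks to 12 months postpartum, so it estimates the 12-month effect minus any effect already present at 6 weeks, not the effect of the whole programme from 29 weeks' gestation

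*Protocol article*

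**What the plan says.** All references are to the protocol article.

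- **Recruitment:** "Upon enrollment, the baseline assessment will be conducted", that is, during pregnancy.
- **Randomisation:** allocation "will occur at ~29 weeks gestation, after completion of the baseline assessment".
- **Methods (opening paragraph):** contacts are used to "deliver the intervention from late pregnancy (29 weeks gestation) to 12 months postpartum, encompassing introductory, active, and maintenance phases". The Discussion likewise presents the trial as a test of a prenatal and postpartum intervention.
- **Lifestyle intervention, Introductory Phase:** before delivery the Lifestyle arm has a face-to-face session, a booster call and mailed print. "The goal of this phase is to optimize gestational weight gain for the remaining pregnancy period", together with preparing women for the postpartum phase.
- **Lifestyle intervention, Active Phase:** this begins at 6 weeks postpartum and "will start with a face-to-face session. The tailoring questionnaires will be repeated".
- **Data analysis:** the main comparison is set out as "Primary analyses will evaluate differences in the change from 6 weeks postpartum to 12 months postpartum between the groups (an intent to treat analysis". This covers weight, insulin-resistance biomarkers and cardiovascular biomarkers. The mixed model is described as "including a common mean at baseline for the treatment groups, a period effect, and an intervention by period interaction". The section does not say which visit is baseline.
- **Outcome variables:** weight loss is measured from weight at delivery.
- **Power and sample size:** the calculation concerns "mean differences in change in outcome variables from baseline".

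**The concern.** The 6-week visit comes after randomisation and after the whole prenatal phase, so weight and biomarkers at that visit are already outcomes of allocation. Measuring change from there subtracts whatever the prenatal phase achieved.

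The Aims section shows the consequence. A woman with normal prepregnancy BMI meets the weight goal by returning to her prepregnancy weight. If the prenatal phase helps her gain less, so that she is back at that weight by 6 weeks and stays there, she is a success under the Aims. Under the primary contrast she contributes zero change. In the other direction, if the Lifestyle arm were worse at 6 weeks and then caught up, the contrast would credit the catching-up as benefit.

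The article also uses three start points: delivery, 6 weeks and baseline. A reader cannot tell which effect the sample size protects. All three primary aims are affected.

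**Working it through.** **1. Timing.** Randomisation is at about 29 weeks. Assuming delivery at 40 weeks, the 6-week visit falls (40 − 29) + 6 = 17 weeks later.

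**2. What the contrast estimates.** Let d6 and d12 be the between-arm differences at 6 weeks and 12 months. The difference in change is d12 − d6. In the planned model with a common mean at enrolment, this is the 12-month interaction term minus the 6-week interaction term. The 12-month term alone is d12.

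**3. The plan's own figure.** Inputs from Power and sample size: 0.35 SD, 128 per arm, 5% level (two-sided assumed).
- Standardised difference: 0.35 × √(128/2) = 0.35 × 8 = 2.80.
- Power: Φ(2.80 − 1.96) = 80%.
- The formula for n gives 129 per arm against the stated 128. Inflating 256 for 15% attrition gives 256/0.85 ≈ 302 against 300.

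The sample-size arithmetic reproduces and is not in question.

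**4. Effect of the subtraction.** The documents give no value for d6. Let f be the share of the 12-month effect D already present at 6 weeks (an assumption). The contrast then targets D(1 − f). With the SD unchanged, power is Φ(8·D(1 − f) − 1.96).

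| f | D = 0.35: target, power | D = 0.40: target, power |
|---|---|---|
| 0 | 0.350 SD, 80% | 0.400 SD, 89% |
| 10% | 0.315 SD, 71% | 0.360 SD, 82% |
| 25% | 0.263 SD, 56% | 0.300 SD, 67% |
| 50% | 0.175 SD, 29% | 0.200 SD, 36% |

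If the early effect is adverse, f is negative. With f = −25%, a true 0.35 SD would be estimated as 0.35 × 1.25 = 0.44 SD.

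**5. Allowing for a smaller SD of change.** The 6-week value may track the 12-month value more closely than a pregnancy value does. For weight, assume SD 15 kg, correlation 0.88 between 6 weeks and 12 months, and 0.85 between enrolment and 12 months.
- SE of raw change from 6 weeks: 15 × √(2 × 0.12) × √(2/128) = 0.92 kg.
- SE of the 12-month difference given enrolment: 15 × √(1 − 0.85²) × √(2/128) = 0.99 kg.

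Suppose the enrolment-anchored analysis has 80% power at 0.35 SD. The 6-week contrast then has power Φ(2.80 × (1 − f) × 0.99/0.92 − 1.96): about 77%, 62% and 33% for f = 10%, 25% and 50%. The loss is smaller than in step 4 but remains. With f = 0 the 6-week contrast would be slightly the more precise of the two.

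**6. If baseline in the model meant the 6-week visit.** The common mean would then force the arms to be equal after treatment had begun. The estimate becomes roughly d12 − ρ·d6, with ρ the within-woman correlation (equal SDs at the two visits assumed). For D = 0.35 and f = 25%:
- ρ = 0.5: 0.35 × (1 − 0.125) = 0.31 SD.
- ρ = 0.9: 0.35 × (1 − 0.225) = 0.27 SD.

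Part of the early effect is still removed, and the constraint has no basis in randomisation.

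**The case against.** **A 6-week start may be deliberate.** The Active Phase begins then, individual goals are set then, the prenatal phase is partly preparation for it, and it is the first non-pregnant measurement. This is plausible, but the article does not say so, and it describes the trial as testing the whole programme. The rationale supports a secondary analysis of the postpartum phase.

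**The contrast is not biased.** A reader might infer that any comparison starting after randomisation is confounded. The documents do not support that. Both visits are outcomes, so among all randomised women the raw difference in change is unbiased for d12 − d6. The fault is that this is a different question.

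**The common mean is probably placed correctly.** A reader might infer that the model equates the arms at 6 weeks. Recruitment and Randomisation put the baseline assessment before allocation, and Outcome variables lists baseline separately from 6 weeks, so enrolment is the more natural reading. Some doubt remains. Data analysis speaks of breastfeeding varying between baseline and follow-up, whereas Table 1 collects it only postpartum.

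**The size is unknown.** This stands. The prenatal contact is modest (one session, one booster call, mailed print), so the early effect could be small.

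**Enrolment values are not like-for-like.** Covariates specifies trained study staff for postpartum weights, while prenatal weights come from prenatal visits. Table 1 lists a 100 g OGTT prenatally and a 75 g OGTT postpartum. This argues against a raw change from enrolment. It does not argue against comparing arms at 12 months given the enrolment value, which needs no common scale.

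**Conclusion.** The point holds. As written, the primary analysis answers what happened between the arms after 6 weeks postpartum, not whether the programme delivered from 29 weeks to 12 months worked. That follows from the stated timing and simple algebra.

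The start points also need reconciling. Outcome variables uses delivery, which is itself after randomisation. Data analysis uses 6 weeks. Power and sample size uses baseline, which Recruitment and Randomisation place before allocation. On that usage the trial is powered for a different contrast from the primary one. If baseline in the power section meant 6 weeks, those two sections would agree with each other, but not with Recruitment and Randomisation.

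The power figures are illustrations under an assumed early effect, not forecasts. They do not show that the trial is underpowered or that 128 per arm is wrong. If there is no effect at 6 weeks, nothing is lost.

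**What to change.** - State in Data analysis that baseline is the pre-randomisation enrolment assessment, and impose the common mean only there.
- Make the primary contrast the between-arm difference at 12 months given the pre-randomisation value (for weight, enrolment or prepregnancy weight). Take it from the same mixed model, with 6 weeks, 6 months and 12 months as outcomes; it is the 12-month intervention-by-period term.
- Keep change from 6 weeks to 12 months as a secondary analysis of the postpartum phase, labelled as such.
- Align the weight-loss definition in Outcome variables and the contrast in Power and sample size with this.

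The choice of covariance structure is a separate modelling preference and is not required for this change.

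**Cost:** wording only, since Table 1 shows that third-trimester values of weight and the biomarkers are already collected. The standard error may be slightly larger, because pregnancy values may correlate less with 12-month values than 6-week values do (0.99 against 0.92 kg under the assumptions above).
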